| MHQ (All Domains)                                                                                                                                                   |           |            |         |                 | ✓                 | ✓                   | ✓                   | ✓                    | ✓                    |
| Hand Function Data Form                                                                                                                                             |           |            |         |                 | ✓                 | ✓                   | ✓                   | ✓                    | ✓                    |
| Participant Payment                                                                                                                                                 |           | ✓          |         | ✓               | ✓                 | ✓                   | ✓                   | ✓                    | ✓                    |
| Adverse Event Collection (if necessary)                                                                                                                             |           | ✓          | ✓       | ✓               | ✓                 | ✓                   | ✓                   | ✓                    | ✓                    |
| Protocol Deviation Collection (if necessary)                                                                                                                        |           | ✓          | ✓       | ✓               | ✓                 | ✓                   | ✓                   | ✓                    | ✓                    |
| RAPA = Rapid Assessment of Physical Activity; MHQ = Michigan Hand Outcomes Questionnaire; SF-36 = Short-Form 36 Questionnaire; MMSE = Mini Mental State Examination |           |            |         |                 |                   |                     |                     |                      |                      |

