- 795 ○ Complication Checklist
- 796 ○ Hand Therapy Data form
- 797 ○ MHQ(all domains)
- 798 ○ Hand function Data Form
- 799 ○ Participant payment

- 800                   ○ Adverse Event collection
- 801                   ○ Protocol deviation collection
- 802
- 803
- 804   Visit 5: Scheduled at 3months following surgery or closed reduction
- 805   Visit 6: Scheduled at 6 months following surgery or closed reduction
- 806   Visit 7: Scheduled at 12 months following surgery or closed reduction
- 807   Visit 8: Scheduled at 24 months following surgery or closed reduction (additional assessment of RAPA
- 808   will be done at this visit)
- 809                   ○ X-Ray
- 810                   ○ SF-36
- 811                   ○ General Health Questionnaire
- 812                   ○ Complication Checklist
- 813                   ○ Hand Therapy Data form
- 814                   ○ MHQ(all domains)
- 815                   ○ Hand function Data Form
- 816                   ○ Participant payment
- 817                   ○ Adverse Event collection
- 818                   ○ Protocol deviation collection

---

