#### 819   8.1.5   FINAL EVALUATION

820   The 8th visit scheduled at 24 weeks following surgery or closed reduction is the final evaluation visit.

821   If the participant is not able to be evaluated within the appropriate time period, the reason should be  
822   noted in the comments section of the participant appointment log and the participant is considered lost  
823   to follow-up for that visit. If possible, the MHQ, SF-36 and RAPA, along with a postage paid envelope,  
824   should be sent to the participant. Despite missing one follow-up visit, the participant is still considered  
825   to be actively enrolled in the study and should be followed up for future visits.

826   Each participant should be reminded at the end of every visit when he/she will need to be seen again  
827   (i.e. "We'll see you in 6 months.") and should schedule an appointment, if possible. If a participant has  
828   not made a clinic appointment within 2 weeks of his/her follow-up date, a member of the research team  
829   should contact the participant via phone to schedule an appointment. The participant should be  
830   reminded that he/she is a valuable member of the research team and that participation is very  
831   important. A participant is considered to be active and should be reminded to return for follow-up  
832   assessment unless he/she chooses to withdraw from the study.

833   In an effort to collected as much data as possible, participants who were enrolled in the study at the  
834   time of their 24-month assessment and who did not complete the assessment will be contacted at the  
835   end of the study (Early 2019). Traditional 24 month surveys (MHQ, SF-36, and RAPA) will be sent to  
836   participants via postal mail.

837

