## 9.2 SAMPLE SIZE DETERMINATION

We propose to randomize 474 patients to one of three surgical arms (158 per surgical arm). We will follow another 158 non-surgical patients meeting the inclusion/exclusion criteria. Sample size was determined to have adequate power for Aim 1 based on the primary outcome of the MHQ summary score at 12-month follow-up. **We expect to have complete data for 12-month follow-up time from 126 patients in each group, after accounting for a conservatively estimated 20% decrease in sample size from losses to follow-up.** For Aim 1, we expect 126 patients per group to give 80% power to detect an 8 point difference in the mean MHQ summary scores between VLPS and CRP and between VLPS and EFP using a mixed-effects model with a two-sided 0.025  $\alpha$ -level test. This assumes a standard deviation (SD) of 18 points (corresponding to an effect size of 0.44 SD), an average of 24 patients per site and an intra-site correlation coefficient (ICC) of 0.012. **To adjust for potential within surgeon correlation, we will also consider either a three level hierarchical model with surgeons nested within site, or use surgeons instead of sites as random intercepts. If technical variation is mostly between surgeons, addressing within surgeon correlation will reduce the ICC, which would give larger power to detect the same effect size. Covariate adjustments will likely give greater power by reducing the variability when the covariates are associated with the outcome and are not highly correlated with other covariates in the model.** We expect the 8 point difference in MHQ score at 12-months as a minimally detectable and meaningful difference between VLPS and either CRP or EFP. Our retrospective study of patients treated with VLPS showed mean ( $\pm$ SD) MHQ scores of 77 ( $\pm$ 15) at 3 months, 81 ( $\pm$ 17) at 6 months, and 85 ( $\pm$ 18) at 12 months for elderly patients. We believe the observed improvement of 8 points from 3 to 12 months to be similar to the expected post-surgical improvement difference between VLPS surgery compared with either EFP or CRP.

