**Missing Data:** We will describe the extent and pattern of missingness in outcome variables by the three groups. Although not expected to be more than 2-3%, we will assess the amount of missing data in baseline covariates as well. If missingness is less than 5% and missing data appear to be at random (e.g., depends on covariates, but not suspected to depend on unobserved outcome) or completely random, we will fit a model using complete data, adjusting for the covariates that missingness is found to depend on. On the other hand, if missingness is greater than 5%, we will impute the missing outcome values based on baseline prognostic factors, and 6-week and 3-month outcome values. Multiple imputation will be implemented using IVEware software, which was developed at the University of Michigan and uses a multivariate sequential regression approach. IVEware can impute all types of data (binary, categorical, count and continuous) and imputes missing values for each individual conditional on all observed values for that individual, and thus exploits correlational structure among covariates that include all other variables observed or imputed. We will then obtain parameter estimates of interest using the described analytic approach in which we will combine the estimates from the five imputed datasets, accounting for both within and between imputation variability.

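### The rule for imputing a missing 12-month MHQ names baseline, 6-week and 3-month values only, conflicts with its own IVEware description, and can bias the primary contrast if 6-month-related loss differs by arm

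*Protocol*

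**What the plan says.** The Missing Data paragraph of section 9.4.2 sets the rule for the outcome: "if missingness is greater than 5%, we will impute the missing outcome values based on baseline prognostic factors, and 6-week and 3-month outcome values". It then says that multiple imputation will be done in IVEware, which "imputes missing values for each individual conditional on all observed values for that individual" and "exploits correlational structure among covariates that include all other variables observed or imputed".

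The Schedule of Activities (section 1.3) has the full MHQ at 6 weeks and at 3, 6, 12 and 24 months. Section 8.1.4 confirms the visit between the last named predictor and the primary time point: "Visit 6: Scheduled at 6 months following surgery or closed reduction", with all MHQ domains. Section 8.1.5 keeps people in follow-up after a gap ("Despite missing one follow-up visit, the participant is still considered" actively enrolled) and plans mailed surveys for those who did not complete the 24-month assessment. Some participants without a 12-month score will therefore have a 6-month score, a 24-month score or both.

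Section 9.2 sizes the trial "after accounting for a conservatively estimated 20% decrease in sample size from losses to follow-up", with complete 12-month data expected from 126 of 158 per arm.

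**The concern.** The named list stops two visits short. It leaves out the 6-month MHQ, which is the last full score before the primary time point. The primary model in section 9.4.2 is a 12-month comparison with site and surgeon effects and has no repeated measures in time, so imputation is the only route by which a 6-month score can inform the primary estimate.

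Imputation is unbiased if loss is random given the predictors used. If people leave because of how they are doing at 6 months, a model that sees only 6 weeks and 3 months does not meet that condition. A difference between arms is plausible here: participants are told their procedure (section 6.4), the outcome is self-reported, and the Aim 2 hypothesis is that VLPS does better at earlier times. At stake is an avoidable error in the primary contrast, and a primary analysis that two statisticians could run differently from the same paragraph.

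**Working it through.** **1. Does the imputation branch apply?** The plan's figures reproduce. With a difference of 8, SD 18, two-sided alpha 0.025 and 80% power:

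- n = 2 × (18/8)² × (2.241 + 0.842)² = 96.2 per arm.
- Design effect = 1 + (24 − 1) × 0.012 = 1.276, and 96.2 × 1.276 = 122.8, close to the stated 126.
- Power at 126/1.276 = 98.7 effective per arm is 0.811.
- 126/0.8 = 157.5, hence 158 per arm.

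The plan therefore expects 158 − 126 = 32 missing 12-month scores per arm, or 20%, against a 5% trigger. The imputation branch is the one expected to apply.

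**2. The two predictor sets**

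| Source in 9.4.2 | 6 wk | 3 mo | 6 mo | 24 mo |
|---|---|---|---|---|
| Named list | yes | yes | no | no |
| IVEware description | yes | yes | if observed | if observed |

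**3. Why the 6-month score matters.** Section 9.4.2 (Aim 2) tries an autoregressive covariance first. With a correlation of 0.7 between adjacent visits, as an example, the 3-month score correlates 0.7² = 0.49 with 12 months and the 6-month score 0.7. Squared, that is 24% against 49% of the variance. Under first-order decay, the earlier scores add nothing once the 6-month score is known.

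**4. Size of the bias if the named list is followed.** The protocol gives no bias figure, so this was simulated with very large arms.

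- From the protocol: five MHQ visits, SD 18, about 20% loss, and a within-person correlation of 0.2 (section 9.2).
- Assumed: loss of the 12-month score is logistic in the 6-month score, with log-odds 1 per SD (odds ratio e¹ = 2.7); correlations above 0.2, either constant or decaying per visit; a 6-month score for everyone; no baseline factors.
- Imputation was by linear regression within each arm, so the result does not turn on whether arm is in the model.

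Scenarios:

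- (a) same mechanism, rates and means in both arms
- (b) same mechanism, comparator 8 points lower (28% against 21% loss)
- (c) same slope, 25% loss in the comparator against 15% in VLPS
- (d) dependence on the 6-month score in the comparator arm only
- (e) opposite dependence in the two arms

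Bias in VLPS minus comparator, in points, with 6-week and 3-month predictors only:

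| Correlation | a | b | c | d | e |
|---|---|---|---|---|---|
| constant 0.2 | 0 | −0.1 | −0.2 | −0.4 | −0.85 |
| constant 0.5 | 0 | −0.2 | −0.3 | −0.5 | −1.1 |
| constant 0.7 | 0 | −0.2 | −0.2 | −0.4 | −0.8 |
| decaying 0.5 | 0 | −0.4 | −0.6 | −1.2 | −2.4 |
| decaying 0.7 | 0 | −0.4 | −0.6 | −1.2 | −2.3 |
| decaying 0.8 | 0 | −0.3 | −0.5 | −1.0 | −1.9 |

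In (a) each arm mean is about 0.4 to 1.2 points too high, but the errors cancel in the difference. In (d) only one arm carries the error. In (e) the two errors add: at correlation 0.2, about 0.42 + 0.42 ≈ 0.85.

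**5. After adding the 6-month score.** The bias is 0.04 points or less in every scenario, which is simulation noise. Adding the 24-month score as well changes nothing material in bias.

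**The case against.** The paragraph says that imputation is based on certain values; it does not say that only those are used. The IVEware sentences then bring in every observed value. On that reading the 6- and 24-month scores are already in the model and nothing is lost. This stands to the extent that the text does not clearly exclude these visits. It does not dispose of the point: one sentence says what this trial will do, the other describes what the software does, and nothing says which governs.

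The larger bias figures also rest on a loss mechanism that the protocol does not suggest, above all opposite dependence in the two arms. That stands too, which is why the range is given by scenario. The simulation further omits the baseline factors on the named list, and it gives everyone a 6-month score. People lost before 6 months have none to contribute, so near-zero bias after the fix is a best case.

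Finally, the Aim 2 longitudinal model uses the 6-month data and offers a cross-check, and imputation detail often sits in a SAP. But Aim 2 is not the primary analysis, and here the protocol itself has named a list.

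**Conclusion.** The point holds as an internal conflict with a possible bias in the primary contrast. If the named list governs, that contrast is off by roughly 0.1 to 1.2 points when arms differ in loss rate, in 6-month mean, or in whether loss depends on the 6-month score in one arm only (at most 1.2/8 = 15% of the target). Opposite dependence in the two arms takes it up to about 2.4 points (30%). At the protocol's own correlation of 0.2, taken as constant, the maximum is about 0.9 points (11%). With the same mechanism, rates and means in both arms it is about 0. The loss mechanisms and the other correlations are assumptions.

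A reader might infer three stronger things that the documents do not support:

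- That the plan definitely discards the 6-month score. The IVEware sentences point the other way.
- That the contrast is biased whenever loss depends on the 6-month result. Without a difference between arms, the errors cancel.
- That leaving out the 24-month score adds bias of this kind. It does not; at most it gives up information.

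The sample size is unaffected. The change should be made because it is cheap and concerns the expected primary analysis.

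**What to change.** In the Missing Data paragraph of section 9.4.2, replace the predictor list with a statement that the imputation model for the 12-month MHQ includes the baseline prognostic factors and all other MHQ assessments (6 weeks and 3, 6 and 24 months). The list then agrees with the IVEware description that follows it. The 6-month score removes this bias for participants who have one; the 24-month score is there only for added information. The cost is one sentence, with no new data, visits or change to the sample size.

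### The imputation rule for the 12-month MHQ leaves the 6-month score off its predictor list and does not match the protocol's own account of what IVEware conditions on

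*Protocol*

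**What the plan says.** The Missing Data paragraph of protocol Section 9.4.2 sets two routes. Below 5% missing, with data judged missing at random, the model is fitted to complete data. Above 5%, "we will impute the missing outcome values based on baseline prognostic factors, and 6-week and 3-month outcome values". Two sentences later the same paragraph says that the software "imputes missing values for each individual conditional on all observed values for that individual". The analysis will then "combine the estimates from the five imputed datasets", accounting for variability within and between imputations.

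Section 9.2 allows for "a conservatively estimated 20% decrease in sample size from losses to follow-up". That takes 158 randomised per arm to 126 with 12-month data.

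The Schedule of Activities (Section 1.3) has a row for "MHQ (All Domains") with ticks at 6 weeks and at 3, 6, 12 and 24 months. At enrolment and 2 weeks only the pain domain is collected. Section 8.1.4 agrees on the full MHQ from 6 weeks onward. Section 8.1.5 keeps a participant who misses one visit in follow-up for later visits.

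**The concern.** The planned loss is four times the 5% trigger, so imputation is the route to expect for the primary endpoint. Only three visits before month 12 yield an MHQ summary score: 6 weeks, 3 months and 6 months. The list names the two earliest and stops. No baseline summary score can make up for this, because none is collected.

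Missing at random is easier to defend given the 6-month score than given the 3-month score. A poor course between 3 and 6 months that leads to drop-out would not enter a model built from the list. If that happened differently in the VLPS, EFP and CRP arms, the primary contrasts would be biased.

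The sentence on IVEware points the other way: conditioning on all observed values would bring in the 6-month score, and the 24-month score where there is one. The paragraph therefore describes two imputation models and does not say which one governs.

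**Working it through.** The endpoint is taken as the MHQ summary score at 12 months, as in Sections 3, 9.2 and 9.4.2.

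**Inputs from Section 9.2:** 158 randomised per arm; 20% loss; difference 8; SD 18; two-sided alpha 0.025; power 80%; 24 patients per site; ICC 0.012; within-person correlation 0.2 (stated there for the longitudinal calculations). Section 9.4.2 (Aim 2) names an autoregressive covariance as the first choice. All other correlations and all drop-out mechanisms below are assumptions.

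**1. The plan's own figure.**
- n before clustering = 2 × (18/8)² × (2.241 + 0.842)² = 96.2, so 97 per arm.
- Design effect = 1 + 23 × 0.012 = 1.276; 97 × 1.276 = 123.8, so 124. The stated figure is 126.
- Power with 126/1.276 = 98.7 effective per arm is 81.1%. The stated figure is 80%.
- 126/0.8 = 157.5, so 158; 3 × 158 = 474.

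The sample size reproduces, and it counts completers only.

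**2. Bias by hand.** Suppose the 20% who drop out of one arm are 1 SD (18 points) worse at 6 months, and the other arm's drop-out is unrelated to outcome. Bias = 0.2 × (true 12-month deficit − deficit predicted from the listed scores).
- Exchangeable correlation 0.2, using 6 weeks and 3 months. The true deficit is 0.2 × 18 = 3.6. The deficit at each listed visit is also 3.6, and each coefficient is 0.2/1.2. The prediction is 2 × (0.2/1.2) × 3.6 = 1.2. Bias = 0.2 × (3.6 − 1.2) = **0.48 points**, 6% of 8.
- Assumed correlations of 0.7 (6 to 12 months), 0.5 (3 to 12) and 0.7 (3 to 6), using 3 months alone: 0.2 × (0.7 × 18 − 0.5 × 0.7 × 18) = 0.2 × (12.6 − 6.3) = **1.26 points**, 16% of 8.

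**3. Bias by simulation.** 300,000 per arm, about 20% drop-out, logit slope of 1 per SD of the 6-month score; correlations 0.2, 0.5 and 0.7, exchangeable or autoregressive by visit. Absolute bias in the 8-point difference:

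| Drop-out depends on 6-month score | Model with 6 weeks, 3 months | 6-month score added |
|---|---|---|
| Alike in both arms | 0.07 or less | 0.07 or less |
| In one arm only | 0.4 to 1.3 (0.45 to 0.59 at correlation 0.2) | 0.04 or less |
| In opposite directions | 0.8 to 2.4 (0.80 to 1.19 at correlation 0.2) | 0.1 or less |

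In the simulation every drop-out has a 6-month score.

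**4. Precision.** Effective n per arm = 126.4/(1 − 0.2 × R²), where 126.4 = 0.8 × 158, baseline factors are ignored, and R² is the share of 12-month variance explained by the scores used.

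| Correlation | R², listed scores | R², adding 6 and 24 months | Effective n | Power |
|---|---|---|---|---|
| 0.2, exchangeable | 0.067 | 0.100 | 128.1 to 129.0 | 81.8% to 82.1% |
| 0.2, autoregressive | 0.002 | 0.077 | 126.4 to 128.4 | 81.2% to 81.9% |
| 0.7, autoregressive (assumed) | 0.240 | 0.658 | 132.8 to 145.5 | 83.3% to 86.8% |

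At assumed correlations of 0.5 to 0.8 the gain is 0.3 to 0.6 power points if exchangeable and about 2.8 to 3.5 if autoregressive.

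**5. Number of imputations.** Relative efficiency = 1/(1 + FMI/m), where FMI is the fraction of missing information. With FMI at most 0.20 it is 0.96 for m = 5, 0.99 for m = 20 and 0.996 for m = 50. Five imputations cost about 1.6 power points or less.

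**The case against.** The strongest reply is that the text does not exclude the 6-month score. The list is not worded as exhaustive, it includes baseline factors, and the IVEware sentence, read literally, admits every observed value. This stands in part. A reader might infer that the 6-month score is certain to be left out; the paragraph does not settle that. The mismatch is itself the defect, because the rule governs the primary endpoint.

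The bias also needs drop-out to depend on the 6-month score differently by arm, and nothing in the protocol predicts that at the size assumed. This stands too. The figures show what could happen and are not a forecast. Equal mechanisms cannot be presumed either, since Sections 2.1 and 2.3.1 describe arms that differ in invasiveness and procedure-specific risks.

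The remedy has limits. Someone lost before 6 months has no 6-month score, and someone lost for good has no 24-month score. A reader might take R² of 0.5 to 0.6 and expect an effective 140 to 144 per arm: 126.4/(1 − 0.2 × 0.5) = 140.4 and 126.4/(1 − 0.2 × 0.6) = 143.6. That assumes every drop-out has the added scores and correlations well above the protocol's 0.2.

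A reader might also infer that the trial is underpowered or that five imputations make inference invalid. Neither follows. Section 9.2 takes no credit for imputation, and the plan combines within- and between-imputation variability.

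**Conclusion.** The point holds in this form: the listed predictors omit the nearest earlier full MHQ and any available 24-month MHQ, and the list does not agree with the IVEware sentence in the same paragraph. With 20% loss planned, the ambiguity falls on the expected primary analysis.

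If the list is followed, one-sided drop-out tied to the 6-month score could bias a VLPS contrast by about 0.5 points at the protocol's correlation of 0.2, or about 1.3 points at assumed correlations of 0.5 to 0.7. The bias could be larger if the dependence ran in opposite directions, and is about zero if drop-out acts alike in the arms. The case for change rests on the credibility of missing at random and on a rule that can be read only one way. Precision is secondary: 0.3 to 0.7 power points at 0.2, and up to about 3.5 at stronger assumed autoregressive correlations. The stated sample size is unaffected, and the number of imputations is a minor matter.

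**What to change.** Reconcile the two sentences in the Missing Data paragraph of Section 9.4.2 with one rule: the imputation model for the 12-month MHQ includes randomised arm, site, the baseline covariates, and the MHQ at 6 weeks, 3 months, 6 months and, where available, 24 months. Reword the IVEware sentence so that it describes that same set.

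Optionally, raise the number of imputations from five to, for example, 20 or more.

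The cost is a sentence or two and some computing time. All the scores are already in the visit schedule, so no new data are needed.

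### Only five imputations are fixed for a primary endpoint with 20% expected missing data: a borderline p-value can cross 0.025 with the seed, and about 1 to 3 points of power are lost

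*Protocol*

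**What the plan says.** The Missing Data paragraph of protocol section 9.4.2 uses complete data if less than 5% is missing and the data appear missing at random. Above 5%, it imputes the missing outcomes from baseline prognostic factors and the 6-week and 3-month outcome values, by sequential regression in IVEware. It then states: "we will combine the estimates from the five imputed datasets, accounting for both within and between imputation variability".

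Section 9.2 gives the expected amount of missing data. It counts 126 of 158 patients per arm as evaluable at 12 months, "after accounting for a conservatively estimated 20% decrease in sample size from losses to follow-up". The primary comparisons are powered "using a mixed-effects model with a two-sided 0.025" test level, with "80% power to detect an 8 point difference in the mean MHQ summary scores between VLPS and CRP and between VLPS and EFP".

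The protocol gives no Monte Carlo error criterion and no provision for raising the number of imputations.

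**The concern.** Twenty percent expected loss is four times the 5% trigger, so the five-imputation branch is what the protocol itself expects to use for its headline result. With m = 5 the between-imputation variance is estimated on 4 degrees of freedom, and the pooled difference is an average of only five random draws.

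Two things are at stake. First, reproducibility: for a result near the threshold, whether it passes 0.025 can depend on the random seed, and a second analyst following the same plan could reach the opposite conclusion. Second, efficiency: the extra variance term and the lower reference degrees of freedom take power from a design that has almost none to spare.

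**Working it through.** **Inputs from section 9.2.** Difference 8 points, SD 18, two-sided alpha 0.025, power 80%, 158 randomised and 126 evaluable per arm, 24 patients per site with ICC 0.012, within-person correlation 0.2. **From section 9.4.2:** m = 5.

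**1. The plan's own figure.** n per arm = 2 × (18/8)² × (2.241 + 0.842)² = 96.2, so 97. The design effect is 1 + 23 × 0.012 = 1.276, and 97 × 1.276 = 123.8, against the stated 126. With 126 per arm the standard error is 18 × √(2 × 1.276/126) = 2.56, and power is Φ(8/2.56 − 2.241) = 81.1% (80.5% with the noncentral t). The stated 80% reproduces, with about one point of slack.

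**2. Fraction of missing information (FMI).** The protocol does not state it, so it is an assumption here. If a proportion p of outcomes is missing at random and the predictors explain R² of the outcome, FMI ≈ p(1 − R²)/(1 − pR²). Two earlier scores with correlation 0.2 to the outcome and to each other give R² = 2 × 0.04/1.2 = 0.067, hence FMI ≈ 0.2 × 0.933/0.987 = 0.19. With R² = 0.6, FMI ≈ 0.08/0.88 = 0.09. The working range is therefore 0.09 to 0.19. The protocol's own correlation points to the upper end. The schedule in section 1.3 also collects only the MHQ pain domain at enrollment, so no full baseline MHQ is available to strengthen the imputation.

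**3. Monte Carlo noise.** The variance of the pooled estimate is (1 + FMI/m) times its value with unlimited imputations, so the noise relative to the pooled standard error is √[(FMI/m)/(1 + FMI/m)].
- FMI 0.09: √(0.018/1.018) = 0.13.
- FMI 0.19: √(0.038/1.038) = 0.19.

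In MHQ points, √(FMI/m) × 18√(2/126) = 0.134 × 2.27 = 0.30 to 0.195 × 2.27 = 0.44. If the design effect is included (2.56 in place of 2.27), this becomes 0.34 to 0.50. With m = 100 the figures are 0.07 to 0.10 (without the design effect).

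**4. Seed dependence.** Take a data set whose p-value with unlimited imputations is exactly 0.025, and pool by Rubin's rules with Barnard-Rubin degrees of freedom. The 95% range of p across seeds is:

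| FMI | m = 5 | m = 20 | m = 50 |
|---|---|---|---|
| 0.10 | 0.011–0.061 | 0.017–0.038 | 0.020–0.032 |
| 0.15 | 0.009–0.079 | 0.015–0.042 | 0.018–0.035 |
| 0.20 | 0.007–0.098 | 0.014–0.047 | 0.017–0.037 |

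If the unlimited-imputation p is 0.02 and FMI is 0.20, five imputations give p < 0.025 for 53% of seeds, against 84% with 50.

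**5. Power.** For a test calibrated to 80% with unlimited imputations, power at m = 5 is 78.9% at FMI 0.09 and 76.5% at FMI 0.19.

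A direct simulation gives the absolute level. It used 158/1.276 = 124 effective patients per arm, 20% missing completely at random, two earlier scores as predictors, an 8-point effect and 6,000 trials per row; 225 imputations stand for unlimited.

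| Within-person correlation | m = 5 | m = 20 | m = 225 | Loss at m = 5 (points) | Two m = 5 runs disagree at 0.025 |
|---|---|---|---|---|---|
| 0.2 (protocol) | 78.0% | 80.7% | 81.2% | 3.2 | 9.7% |
| 0.4 | 79.5% | 81.9% | 82.3% | 2.7 | 8.7% |
| 0.6 | 82.8% | 84.1% | 84.4% | 1.6 | 6.2% |

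The simulation standard error of the loss is about 0.3 points. Among trials whose p with 225 imputations lay between 0.02 and 0.03, two runs with m = 5 disagreed in 46 to 51%.

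**The case against.** The strongest reply is that nothing here is invalid. Rubin's rules allow for a finite number of imputations; the type I error at m = 5 is about 0.024 against a nominal 0.025, and the estimate is unbiased. That stands: the point is about efficiency and reproducibility, not validity.

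Several qualifications also stand.
- The wide p-ranges apply only to results already near the threshold. Under the planned effect, two runs disagree in about 6 to 10% of all trials, and under the null in 1.2 to 1.9%. Sampling error (about 2.6 points) is far larger than the Monte Carlo noise.
- The 4 degrees of freedom belong to the between-imputation variance, not to the test. The test has about 156, 95 and 62 at FMI 0.09, 0.14 and 0.19, and the interval is only about 1.3, 2.4 and 3.8% wider than with unlimited imputations.
- FMI is assumed. The protocol calls its 20% conservative and allows surveys by mail, email or phone, so actual loss may be lower. At FMI 0.05 the power loss is about 0.3 points.
- Power at m = 5 can still exceed 80% if the earlier scores predict well (84.5% at FMI 0.10). The loss relative to more imputations remains.
- The 0.025 level is stated in the sample-size section, whereas section 9.4.2 promises 95% confidence intervals. Seed dependence arises at any threshold.

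A statistical analysis plan that is not shown may fix a seed. That would make one run repeatable, but it would remove neither the dependence on which seed was chosen nor the power loss.

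**Conclusion.** The concern holds. On the protocol's planning figure of 20% missing, five imputations govern the primary analysis. For FMI between 0.09 and 0.19 they add Monte Carlo noise of 0.13 to 0.19 standard errors, cost about 1 to 3 points of power, and leave a borderline result dependent on the seed. With the protocol's own within-person correlation of 0.2 the power loss is about 3 points, which takes the primary test from 81.2% to 78.0%, below the stated 80%.

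These sizes rest on the assumed FMI, on data missing at random and on loss near 20%. The issue disappears if less than 5% is missing and the data appear missing at random, because complete data are then used. The change should be made, though the trial's validity does not depend on it.

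**What to change.** In the Missing Data paragraph of section 9.4.2, replace five with at least 50 imputed datasets, preferably 100. Record the random seed before the analysis, and report the Monte Carlo error of the primary difference and of its p-value; the seed and the error reporting can sit in the statistical analysis plan. At FMI 0.19 to 0.20, a p-value of 0.025 would then range over about 0.017 to 0.037 with 50 imputations, and over about 0.019 to 0.033 with 100.

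The cost is one number in the text and some minutes of computing. The imputation model, the estimand, the visits and the number of patients stay as they are, and there is no downside.
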